## **10.2 Sample Size**

This Phase 1 trial is not powered to detect statistically significant differences between groups. Even though comparative statistics for the safety variables will be computed, the study will have low power to detect anything other than very large differences in the incidence of local injection site and systemic side effects between the vaccination groups. This is done weighing the need to detect any possible untoward reactions against the need to limit the number of volunteers involved for safety purposes. The sample size of 102 for this study is within the range commonly used in Phase 1 trials for the initial assessment of the safety, tolerance and immunogenicity of an investigational vaccine. Incorporation of a comparator vaccine will enable broad initial estimates of the incidence of local injection site and systemic side effects and of immune responses among vaccine recipients.

## **11 PROTECTION OF HUMAN SUBJECTS**

### **11.1 Institutional Review Boards**

The investigators will be responsible for obtaining IRB approvals for the study. Before the start of the study, the appropriate documents (including the protocol, Investigator's Brochure, and informed consent form) will be submitted to the IRBs. Full approval for the study will be obtained from the CPqRR and George Washington University Medical Center IRBs.

The study will be conducted according to the Declaration of Helsinki, the US Code of Federal Regulations (Protection of Human Subjects [21 CFR 50], Institutional Review Boards [21 CFR 56], and Obligations of Clinical Investigators [21 CFR 312]) and Brazilian Resolution N° 196/96 on Research Involving Human Subjects.

Modifications to the protocol will not be implemented without prior written IRB approval except when necessary to eliminate immediate hazards to the participants. The IRBs will be informed by the Investigator of any new information that may adversely affect the safety of the subjects or the conduct of the study, an annual update and/or request for re-approval, and when the study has been completed.

### **11.2 Informed Consent**

The principles of informed consent in the current edition of the Declaration of Helsinki will be implemented prior to any protocol-specified procedures being conducted. Informed consent will be obtained in accordance with US 21 CFR 50.25 and Brazilian Resolution N° 196/96 on Research Involving Human Subjects.

Informed consent will be documented by the use of a written consent form approved by the IRBs. All relevant information will be provided in both oral and written form in a way that is understandable to the subject. Ample time and opportunity will be given for the participant to inquire about details of the study. Subjects unable to read will place an imprint of their finger/thumb in the place of a signature; in addition, an independent witness, who is not a

member of the study team, will sign the consent form to attest that the volunteer comprehended the contents.

The Principal Investigator (or the Investigator's designee) will explain the nature of the study and will inform the subject that participation is voluntary and that they can withdraw at any time. The volunteer will be informed about the study's purpose, goals, expected benefits and risks, and potential risks that are currently unforeseeable. They will be provided with a description of the procedures and an estimated duration of time that will be required to participate in the study, and they will be informed of alternatives to participation in the study. The volunteers will receive an explanation as to what medical treatments are available if injury occurs as a result of participation in the study and whom to contact in the event of a study-related injury. They will also be informed whom they should contact for answers to any questions relating to the study. The volunteer will be informed that his/her signature or fingerprint on the informed consent form indicates that he/she has decided to participate in the study having discussed the information presented.

The original signed informed consent form for each volunteer will be maintained as part of the volunteer's study records by the Principal Investigator. A copy of the informed consent form will be provided to every volunteer.

### **11.3 Risks**

Risks to the participants are those associated with venipuncture and with immunization. These risks are outlined below.

Female participants will be cautioned of the unknown risk of the *Na-GST-1/Alhydrogel*® or *Na-GST-1/GLA-AF* vaccines to the fetus. Females of childbearing potential, unless surgically sterile (i.e., bilateral tubal ligation, bilateral oophorectomy, or complete hysterectomy), is at least 2 years postmenopausal, or practices abstinence, must use 2 effective methods of avoiding pregnancy (including oral, transdermal, or implanted contraceptives, intrauterine device, female condom with spermicide, diaphragm with spermicide, cervical cap, or use of a condom with spermicide by the sexual partner) until at least one month following the last immunization. Female participants will be counseled by a study clinician or nurse, or referred to the local health center for evaluation and institution of an appropriate contraceptive method.

#### ***11.3.1 Venipuncture***

Risks occasionally associated with venipuncture include pain and bruising at the site of venipuncture, lightheadedness, and syncope (rarely).

#### ***11.3.2 Immunization with Na-GST-1/Alhydrogel*®**

Possible local vaccine reactions include pain, swelling, erythema, induration, transient limitation of limb movement, lymphadenopathy, or pruritus at the injection site. Local subcutaneous nodules, believed to be granulomatous reactions to aluminum hydroxide, have been observed with use of aluminum hydroxide-based adjuvants. Thus, most aluminum hydroxide-adsorbed vaccines are injected intramuscularly rather than subcutaneously. Systemic reactions such as fever, headache, malaise, myalgia, and joint pain, may also possibly occur. Immediate

hypersensitivity reactions including urticaria, anaphylaxis, or other IgE-mediated responses are possible as with any vaccine. As with any investigational vaccine, there is a theoretical possibility of risks about which we have no present knowledge. Participants will be informed of any such risks should further data become available.

### ***11.3.3 Immunization with Na-GST-1/Alhydrogel® plus GLA-AF***

The possible local vaccine reactions to be expected are similar to those of Na-GST-1/Alhydrogel® administered without GLA-AF. However, in a study of another vaccine administered with GLA-SE (a formulation similar to GLA-AF), the frequency and intensity of local reactions were somewhat greater than when the vaccine was administered without GLA-SE.

### ***11.3.4 Immunization with Butang®***

Recombinant hepatitis B vaccines have been administered to millions of people worldwide and have an established safety record. Adverse reactions may be local and include erythema, warmth, edema, induration with or without tenderness as well as urticaria, and ecchymosis. Malaise, transient fever, hypotension, nausea, diarrhea, headache, and arthralgia may develop in some patients after the injection. An apparent hypersensitivity syndrome (serum-sickness-like) of delayed onset has been reported days to weeks after vaccination, including: arthralgia/arthritis (usually transient), fever, and dermatologic reactions such as urticaria, erythema multiforme, ecchymoses and erythema nodosum. On very rare occasions, non-fatal anaphylaxis has been reported following administration of recombinant hepatitis B vaccines.

## **11.4 Precautions taken to Minimize Risks**

As outlined above, the participants will be monitored closely during their participation in this study. The study vaccines have been produced according to current Good Manufacturing Practices (cGMP). The vaccines will be administered by experienced investigators with drugs and equipment available for the treatment of anaphylaxis and other potential adverse reactions. All vaccine doses will be given by intramuscular injection to minimize injection site reactions such as pain. Furthermore, to reduce the likelihood of immediate-type allergic reactions to the Na-GST-1 vaccine formulations, all potential trial participants will be screened for detectable IgE to Na-GST-1; individuals with detectable IgE antibodies to the vaccine antigen by the ELISA assay that are confirmed to be >0.35 kUA/L by the ImmunoCAP method as described in **Section 7.8**, will be excluded from participation in the study.

## **11.5 Benefits**

Participants may not receive any direct benefit from participation in this study. It is hoped that information gained in this study will contribute to the development of a safe and effective hookworm vaccine. Participants who receive Butang® during the course of the study proper may receive the benefit of subsequent protection against exposure to the hepatitis B virus. These participants will be tested for antibodies to the hepatitis B surface antigen using serum collected during the Day 380 visit. If a participant does not have protective levels of anti-hepatitis B surface antigen antibodies, they will be offered a second series of the vaccine using the manufacturer-recommended 0, 1, and 6-month vaccination schedule. This will be offered after the final study visit and at no charge to the participant. Participants who receive either of the Na-

GST-1 formulations during the trial will be offered Butang® hepatitis B vaccine after the conclusion of the study, and thus may also receive this benefit.

All participants in Part II of the study will undergo a stool examination for ova and parasites at the Day 140 and Day 380 study visits. Those found to have a helminth infection at either of these study visits will be offered appropriate treatment at the conclusion of the study, free-of-charge.

Free medical treatment will be provided to all enrolled participants during the active immunization phase and the follow-up period. If the investigators judge that a participant requires hospitalization, transportation will be arranged and the medical management of the participant will be monitored by a study physician and the local Medical Monitor. Medical care for ailments not related to vaccination will not extend beyond the study period, but will be referred to the nearest government-run health clinic. Medical care for ailments related to vaccination will extend at least until the condition has resolved or stabilized (if a chronic condition).

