Screening steps 3-8 must be performed within 90 days of the planned enrollment into the study. Should this screening window be exceeded before the first vaccination, screening procedures (not including administration of the informed consent form or comprehension questionnaire) may be repeated to ensure continued eligibility for the study (screening procedures can be repeated a maximum of one time).

Any clinically relevant finding that is discovered upon screening will be treated appropriately according to the standard of care in Brazil, as follows. Initial management will be performed at the study clinic, free of charge. Should referral for more extensive investigation or treatment be required, the study will arrange and pay for transportation to a government healthcare facility and initial consultation. Initial care – according to the standard of care in Brazil – will be covered; however, in the event that a chronic illness is discovered during the course of screening, long-term treatment and care will not be reimbursed by the study, but the individual will be referred to the local health authorities for appropriate treatment and follow-up.

If the fecal exam performed during screening demonstrates infection with an intestinal parasite the individual will be treated with an appropriate medication prior to being enrolled in the study and before any vaccinations. Volunteers in Part I of the study will be excluded if infected with hookworm at screening. Individuals infected with *Ascaris lumbricoides* or *Trichuris trichiura* will be treated with a single 400 mg oral dose of albendazole; three 400 mg doses of albendazole will be given to individuals infected with hookworm; individuals infected with *S. mansoni* or *Taenia* spp. will be treated with a single 60 mg/kg oral dose of praziquantel; and, individuals

infected with *Strongyloides stercoralis* will be treated with three 400 mg daily oral doses of albendazole.

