6. Observe for at least 2 hours after vaccination to evaluate for immediate adverse reactions. During the 2-hour post-immunization wait period, study staff will discuss signs and symptoms of potential AEs.

Study Day 113 (1 day after Third Vaccination)

1. Perform basic history and physical exam (including injection site), emphasizing examination of any acute complaints.
2. Record vital signs.

Study Day 115 (3 +/- 1 days after Third Vaccination)

1. Perform basic history and physical exam (including injection site), emphasizing examination of any acute complaints.
2. Record vital signs.

Study Day 119 (7 +/- 1 days after Third Vaccination)

1. Perform basic history and physical exam (including injection site), emphasizing examination of any acute complaints.
2. Record vital signs.

Study Day 126 (14 +/- 2 days after Third Vaccination)

1. Perform basic history and physical exam (including injection site), emphasizing examination of any acute complaints.
2. Record vital signs.
3. Obtain blood for hematology, biochemistry, anti-GST-1 and total IgE antibody ELISAs, and cellular immunology assays.

Study Day 140 (28 +/-4 days after Third Vaccination)

1. Perform basic history and physical exam, emphasizing examination of any acute complaints.
2. Obtain blood for anti-GST-1 and total IgE antibody ELISAs and cellular immunology assays.
3. Obtain stool for examination for ova and parasites (Part II only).

Study Day 200 (3 months +/-14 days after Third Vaccination)

1. Perform basic history and physical exam, emphasizing examination of any acute complaints.
2. Obtain blood for anti-GST-1 and total IgE antibody ELISAs and cellular immunology assays.

Study Day 290 (6 months +/-14 days after Third Vaccination)

1. Perform basic history and physical exam, emphasizing examination of any acute complaints.
2. Obtain blood for anti-GST-1 and total IgE antibody ELISAs and cellular immunology assays.

Study Day 380 (9 months +/-21 days after Third Vaccination)

1. Perform basic history and physical exam, emphasizing examination of any acute complaints.
2. Obtain blood for anti-GST-1 and total IgE antibody ELISAs.
3. Obtain stool for examination for ova and parasites (Part II only).

Study Day 470 (12 months +/- 21 days after Third Vaccination)

1. Perform basic history and physical exam, emphasizing examination of any acute complaints.

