### **7.9 Stool Examination**

Fecal exams will begin with an ether sedimentation assay to determine infection status (positive or negative). In Part II of the study, positive samples will undergo Kato Katz fecal thick smear exams to determine infection intensity (eggs per gram of feces).

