## **8.2 Assessment of Adverse Events**

### **8.2.1 Identification of AEs**

Assessment of safety will include clinical observation and monitoring of hematological, blood chemistry, and immunologic parameters. Safety will be evaluated by monitoring of participants for local and systemic adverse reactions during the course of the trial. Participants will be closely monitored for at least 2 hours following each immunization. Additionally, participants will be evaluated on Days 1, 3, 7, 14 and 28 following each vaccination for clinical assessments.

All AEs will be graded for severity and relationship to study vaccine. Reactions will be graded as described in **Section 8.2.2** in this protocol. During Part II of the study, a study clinician will stay in or near Americaninhas for the duration of the trial and will be available to the study participants at all times. Should a participant call on a study clinician to report an AE, it will be fully documented in their study chart, and discussed with the Principal Investigator.

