## **8.6 Treatments That Could Potentially Interfere with Vaccine-Induced Immunity**

The following criteria will be checked at each visit. If any are reported during the study, the participant will be excluded from receiving further doses of the study vaccine and will not be included in the immunogenicity evaluations after the time of exclusion. The participant will, however, be encouraged to remain in the safety evaluation for doses already received.

1. Use of any investigational drug or investigational vaccine other than the study vaccine during the study period.
2. Administration of chronic (defined as more than 14 days) immunosuppressants or other immune-modifying drugs up to 30 days after the last dose of vaccine. (Topical and nasal steroids are allowed.)
3. Administration of immunoglobulins and/or any blood products up to 30 days after the last dose of vaccine.

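### Section 11.5 puts off the offer of treatment for helminths found at Day 380 to an undefined study conclusion, which protects no scheduled data; for Day 140 findings it states neither a reason nor an exception

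*Protocol*

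**What the plan says.** Section 11.5 of the Protocol schedules stool examinations for all Part II participants at Day 140 and Day 380 and then fixes when a finding is acted on: "Those found to have a helminth infection at either of these study visits will be offered appropriate treatment at the conclusion of the study", free of charge. The protocol does not say whether this means the participant's own last visit or the end of the whole trial. The Day 140 and Day 380 visit lists in Section 7.6, Section 7.9 and Appendix B contain no earlier treatment step.

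Other parts of the protocol bear on the point:

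- Section 7.2, on an intestinal parasite found at screening: "the individual will be treated with an appropriate medication prior to being enrolled in the study". Regimens are given by species.
- Section 7.9, on Part II stool: "positive samples will undergo Kato Katz fecal thick smear exams to determine infection intensity".
- The next paragraph of Section 11.5: "Free medical treatment will be provided to all enrolled participants during the active immunization phase and the follow-up period".
- Section 8.2.1: "a study clinician will stay in or near Americaninhas for the duration of the trial".
- Section 7.6, Day 126, the last visit with a blood count: "Obtain blood for hematology, biochemistry, anti-GST-1 and total IgE antibody ELISAs, and cellular immunology assays".
- Section 8.6 lists treatments that end vaccination, after which a participant "will not be included in the immunogenicity evaluations after the time of exclusion". Anthelmintics are not on the list.

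**The concern.** A participant can have a known, treatable infection on file while the protocol's specific instruction is to wait. Section 1.1 ties hookworm intensity to blood loss and names women of reproductive age among the most vulnerable; women aged 18 to 45 are eligible. No hemoglobin measurement is scheduled after Day 126, so nothing routine would show a fall during the wait. A delay of this kind needs a purpose, such as protecting an endpoint, and the protocol states none. The question is whether the sampling schedule supplies one, and the answer differs between the two stool visits.

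**Working it through.** **Length of the wait (Sections 7.6, 4.2 and 11.5, Table 3).** The protocol states no figure to reproduce.

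- To the participant's Day 470 visit: 470 − 140 = 330 days; 470 − 380 = 90 days.
- Visit windows, counted from the third vaccination (Day 112), put the visits at 28 ± 4, 268 ± 21 and 358 ± 21 days.
  - Day 140 finding: (358 − 21) − (28 + 4) = 305 to (358 + 21) − (28 − 4) = 355 days.
  - Day 380 finding: (358 − 21) − (268 + 21) = 48 to (358 + 21) − (268 − 21) = 132 days.
- If the last Part II participant's final visit is meant, Cohort 12 starts at least 5 weeks (35 days) after Cohort 7. For Cohort 7 the wait is then at least 330 + 35 = 365 and 90 + 35 = 125 days.

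**What the wait could protect (Sections 2, 7.6 and 10.1.1, Appendix B).**

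| Scheduled item | Last time point | After Day 140? | After Day 380? |
|---|---|---|---|
| Main IgG comparison | Day 126 | no | no |
| Blood count | Day 126 | no | no |
| Cellular assays | Day 290 | yes | no |
| Antibody ELISAs | Day 380 | yes | no |
| Stool examination | Day 380 | yes | no |
| History and physical | Day 470 | yes | yes |

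No objective is an infection outcome. Once the Day 380 samples are taken, an anthelmintic cannot affect any scheduled laboratory or stool result. After Day 140 it could affect the antibody samples at Days 200, 290 and 380, the cellular samples at Days 200 and 290, and the Day 380 stool result.

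**How many participants (rough illustration).** Inputs are 66 Part II participants, the site rate of about 300 post-treatment infections per 1,000 per year (Section 3), and the 5 to 9 weeks to adult worms (Section 1.1). The formula is 66 × (1 − exp(−h × (t − lag)/365)), with h = 0.3, or h = −ln(0.7) = 0.357 if the figure is read as an annual risk.

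| h | Lag (days) | By Day 140 | By Day 380 | Difference |
|---|---|---|---|---|
| 0.300 | 0 | 7.2 | 17.7 | 10.5 |
| 0.300 | 35 | 5.5 | 16.3 | 10.8 |
| 0.300 | 63 | 4.1 | 15.1 | 11.0 |
| 0.357 | 0 | 8.4 | 20.5 | 12.1 |
| 0.357 | 35 | 6.4 | 18.9 | 12.5 |
| 0.357 | 63 | 4.8 | 17.6 | 12.8 |

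This gives about 4 to 8 new infections by Day 140 and roughly 11 to 13 more by Day 380. Most new infections would therefore face the 90-day wait and not the 330-day one. In addition, at least 6 × 4 = 24 of 66 enter with hookworm found at screening or documented within 3 months of first vaccination (Section 4.2). Any infection that survives treatment could also be found at Day 140; that number cannot be estimated from the protocol.

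**The case against.** The strongest reply concerns Day 140. Secondary Objective 2 is the duration of the antibody response, and Section 1.13.1 warns that natural exposure complicates immunogenicity data in endemic areas. Treating every Day 140 positive at once would remove worms selectively, in participants picked out by infection status after randomization, during the Day 200 to 380 follow-up. Part II has 10 participants per dose and formulation and 6 on the comparator. With 4.1 to 8.4 new infections in 66, a group of 10 would contain about 4.1/6.6 = 0.6 to 8.4/6.6 = 1.3 of them. A recorded treatment date could hardly support an adjustment on that basis. This stands: immediate treatment of all Day 140 positives is a trade-off for the sponsor and the IRBs. The omission of anthelmintics from Section 8.6 does not settle it, because that list concerns further doses and exclusion from immunogenicity evaluation.

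The reply has no force for Day 380, where nothing remains to be sampled.

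The second reply is that care is already provided: free medical treatment, a clinician nearby, and history and physical visits through Day 470. This stands for recognised illness. A reader might infer from Section 11.5 that ill participants are left untreated; the free-care promise does not support that. But it is a general promise beside a specific sentence on stool findings, and the text does not reconcile the two. For an infection without recognised illness, the specific sentence governs.

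A reader might also see a contradiction with Section 7.2. There is none: that rule applies at entry, before follow-up begins, and a different rule can hold later.

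**Conclusion.** The point holds in a limited form. Section 11.5 defers the treatment offer to an undefined time, nominally Day 470 at the earliest, without giving a reason. For infections found at Day 380 the delay is nominally 90 days (48 to 132 within visit windows), or at least 125 days for Cohort 7 on the later reading, and it protects no scheduled data. For infections found at Day 140 a reason can be inferred, but the protocol neither states it nor makes an exception for an infection that warrants earlier treatment.

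It is tempting to conclude that participants will be harmed by an 11-month delay. The documents do not support that. The 330-day wait applies only to Day 140 positives. Section 1.1 places hookworm disease mainly in moderate and heavy infections, and the protocol does not say how many later infections would be of that kind. Hemoglobin limits at entry and treatment at screening also lower the risk.

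The lengths of the waits follow from the visit schedule. The counts of infected participants assume a constant rate, all participants clear at Day 0, full retention and perfect detection, and serve only as illustration. This is a low-cost improvement in participant safety.

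**What to change.** Amend Section 11.5 as follows:

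- **Day 380 findings:** offer the Section 7.2 regimens, free of charge, as soon as the result is known.
- **Day 140 findings:** offer the same regimens no later than just after the Day 380 samples are taken. The nominal maximum wait falls from 330 to 380 − 140 = 240 days.
- **Exception:** state that the deferral does not prevent earlier treatment of a Day 140 infection when the egg count already measured under Section 7.9, or the study clinician's assessment, calls for it. The protocol gives no egg-count threshold, so the amendment should set one or leave the decision to the clinician.
- **Record:** enter the treatment date on the CRF.

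The cost is a few sentences and one CRF field, submitted as an amendment with sponsor and IRB approval under Section 9.4. Treatment is already promised free of charge, so only its timing changes. The downside is that the few Day 140 positives treated early would have anthelmintic exposure during the Day 200 to 380 antibody follow-up. The recorded date would identify them, although in groups of this size it would not support a real adjustment.
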